## Methods

### Study design

The MEDPass Trial is a randomized, controlled, clinical trial (RCT) conducted with parallel groups. Blinding of patients is not possible because of the evident differences in ONS administration times. Therefore, it is conducted as an open-label RCT. The MEDPass Trial is a superiority trial. The allocation ratio of intervention group and control group is 1:1.

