### Study population

The MEDPass Trial includes medical as well as geriatric inpatients at the Tiefenau facility of the University Hospital of Bern. It includes inpatients of the Department of Geriatrics and the Department of General Internal Medicine who meet the eligibility criteria listed in Table 1.

**Table 1 Tab1:** Inclusion and exclusion criteria

**Inclusion criteria**	• Nutritional Risk Screening (NRS 2002) total score ≥ 3 points according to routine screening at admission within 72 h [25] • Expected hospital LOS ≥ 3 days after screening (as estimated by the treating physician) • Patient qualifies for ONS and approves prescription • Age > 18 years • Willingness and ability to provide informed consent
**Exclusion criteria**	• Initially admitted to critical care unit • Immediate post-operative phase (< 7 days post-surgery) • Dysphagia with the inability to swallow liquids • Admitted with or scheduled for supplemental or total enteral nutrition and/or parenteral nutrition • Mini Mental State examination < 16 points • Hospitalization due to anorexia nervosa, acute pancreatitis, or acute liver failure • Patients with cystic fibrosis, short bowel syndrome, or after gastric bypass surgery • Terminal condition (end of life situation) • Poor German language skills (study language)

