#### Baseline patient characteristics and procedural variables

The following baseline patient characteristics are recorded by RDs during visit 1 (Table 2):
✓ Disease categories for main diagnosis (gastrointestinal disease, infectious disease, cardiovascular disease, neurological disease, oncologic disease, other diseases)✓ Department in which the patient is hospitalized✓ Gender (male, female)✓ Age (years)✓ Energy content per ml ONS (1.5 kcal/ml or 2 kcal/ml)✓ NRS 2002 total score✓ NRS 2002 subscore for impaired nutritional status✓ Body weight (kg)✓ Body height (cm)✓ BMI (kg/m^2^)

The following procedural variables are recorded after discharge by one of the co-investigators:
✓ Number of days from trial inclusion to hospital discharge✓ Number of days with prescribed ONS✓ Number of days with energy and protein intake monitoring✓ Compliance versus non-compliance with the study protocol✓ Number of meals at which patients were nil per os during energy and protein intake assessment (meals at which patients are not allowed to eat for medical reasons)✓ Number of meals at which food intake could not be assessed✓ Involvement of RDs in the treatment of the patients

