#### Sample size calculation

Based on our clinical experience, we assumed for our power analysis that administration of ONS in the MEDPass mode increases energy intake (primary endpoint) by at least 10% (i.e., by 200 kcal from an average of 2000 kcal/day). Furthermore, we assumed that an average patient weighs 75 kg and therefore has an approximate energy requirement of 2200 kcal. A final assumption is that in current clinical practice they may only receive 2000 kcal/day. Therefore, to demonstrate that intervention group patients have an increased average daily energy intake of 200 kcal/day (i.e., from 2000 (SD 500 kcal) to 2200 (SD500 kcal)), we need to include 200 patients to achieve 80% power (alpha error of 0.05). The power calculation used the sampsi command in STATA® (Stata Corp, USA, 2017, version 15.3). Importantly, this trial is not powered to investigate whether the difference in energy intake of 200 kcal/day makes a significant difference to clinical outcomes. However, a similar increase in energy intake has previously shown to decrease the risk of adverse outcome and mortality [7].

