#### Primary analysis

The baseline patient characteristics will be summarized for both groups. The primary analysis will be performed as an intention-to-treat (ITT) analysis including all randomized patients regardless of protocol adherence. In a further step, we will also do a per-protocol analysis excluding patients with major protocol violations as outlined below.

For the primary outcome, we will test whether MEDPass administration is superior to usual care and compare the average amount of daily energy intake using a Student’s *t* test or chi-square test. We will also fit linear regression models adjusted for initial NRS 2002 score and average amount of energy in the ONS, reported adjusted differences (coefficients), and corresponding 95% confidence intervals (CIs). Total energy, protein, and ONS intake throughout the study period will be divided by days of assessment per patient. Linear regression analysis adjusted for stratification factors will also be used for the evaluation of average daily protein intake as compared to the individual requirement (%) throughout the hospitalization, average intake of ONS/day (ml) throughout the hospitalization, and hospital LOS (days) between the groups. Logistic regression analysis adjusted for stratification factors will be is used for difference in 30-day mortality (yes/no) between the groups. Repeated measure models will be used for the evaluation of differences in course of handgrip strength throughout the hospitalization, weight changes throughout the hospitalization, and course of appetite and nausea throughout the hospitalization. The procedural variables will be analyzed and presented descriptively. There will not be a statistical safety assessment since there are no safety endpoints in the MEDPass Trial. Safety events will be presented descriptively.

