The stratification of randomization is aimed at preventing statistical differences between groups due to ONS energy density. This is a relevant approach since differences between groups would directly affect the primary outcome. Furthermore, the stratification for NRS 2002 score is aimed at reducing differences in nutritional risk between groups. This may reduce bias significantly and therefore all statistics will be adjusted for both stratification factors. The wide selection of ONS available in the institution represents daily clinical practice. There is no influence of the financial sponsor on the selection of ONS in this study.

Our initial calculation and projections predicted the completion of patient recruitment in spring 2020. In the course of the trial, recruiting was prolonged for various reasons, including predominantly organizational barriers to recruitment. Organizational barriers are frequently described as significant for the prolongation of clinical trials [40–42]. In patients with unscheduled admissions, such as the majority of those in our facility’s medical department, recruitment challenges are more evident. LOS in the medical department is usually shorter than on the geriatric wards. This disqualifies some of the medical patients because after screening and referral, they may not stay three more days as needed according to the eligibility criteria. Moreover, medical patients with unscheduled hospitalizations may be too anxious about their treatment, in pain, or too unwell to provide consent [42]. Recruitment on the geriatric wards also presents challenges. Reading and understanding the consent forms may be difficult for some of the patients [41]. Furthermore, distrust and/or fatigue are known barriers in recruiting elderly patients onto clinical trials [41].

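### Prespecifying age, and secondarily department, as covariates in the primary regression would be a nearly free gain in precision; leaving them out is not an error

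*Protocol article*

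**What the plan says.** The trial pools two departments (Study population): "It includes inpatients of the Department of Geriatrics and the Department of General Internal Medicine". Randomization is stratified by NRS 2002 score in three levels and by ONS energy density in two. In the section Primary analysis, the adjusted model for the primary outcome uses those same two factors: "We will also fit linear regression models adjusted for initial NRS 2002 score and average amount of energy in the ONS". The Discussion adds that every analysis is to be adjusted for both stratification factors.

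The baseline list includes age and "Department in which the patient is hospitalized". Neither is a stratification factor, a covariate or a listed subgroup.

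The primary outcome is average daily energy intake, given in kcal and as a percentage of the calculated requirement (Outcomes). The requirement formula depends on age and BMI (Energy, protein, and ONS intake; Table 3). On the departments, the Discussion says "LOS in the medical department is usually shorter than on the geriatric wards", and LOS is assessed in medical inpatients only because geriatric stays have a fixed length.

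The article describes the primary test in two ways. The Abstract calls the primary analysis adjusted for the stratification factors. The section Primary analysis names a t test or chi-square test first and adds the regression as a further step.

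**The concern.** A baseline variable that predicts the outcome and is left out of the model leaves its variance in the error term, and any chance imbalance in it goes uncorrected in the estimate. The protocol's own reason for stratifying is that the chosen factors may directly influence the outcomes. The same reasoning applies to age, because the requirement that forms the denominator of the percentage outcome changes at 65. It may also apply to department. What is at stake is a few points of power in a trial planned at just over 80%, whose recruitment has already been prolonged.

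**Working it through.** **The plan's own figure.** Inputs from Sample size calculation: difference 200 kcal/day, SD 500 in each arm, alpha 0.05, power 80%. Allocation is 1:1 (Study design). Two-sided:

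n per arm = 2 × (1.960 + 0.842)² × 500² / 200² = 98.1, rounded up to 99, so 198 in total.

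This agrees with the stated 200. At 100 per arm the standard error is 500 × √(2/100) = 70.7 kcal and power is 80.4% (noncentral t; 80.7% by the normal approximation).

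**The age step on the percentage scale.** Inputs: Table 3 for BMI above 18.5, and the 75 kg patient and 2000 kcal intake from Sample size calculation.

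- Under 65: 75 × 27 = 2025 kcal; 2000/2025 = 98.8%.
- Over 65: 75 × 30 = 2250 kcal; 2000/2250 = 88.9%.
- Gap: 9.9 percentage points.
- Target effect: 200/2200 = 9.1 points. SD: 500/2200 = 22.7 points.

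With a share p of patients under 65, the variance explained is R² = p(1−p) × gap² / SD². At an assumed p = 0.5 this is 0.25 × 9.9² / 22.7² = 4.7%. At p = 0.3 it is 4.0%, and at p = 0.2 it is 3.0%. These figures assume that intake in kcal and body weight are the same on both sides of 65.

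**Department, in kcal.** The article gives neither the split between departments nor any difference in intake, so both are assumed. With a 50:50 split, R² = 0.25 × d² / 500²:

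| Assumed ward gap d (kcal/day) | R² |
|---|---|
| 0 | 0% |
| 100 | 1% |
| 200 | 4% |
| 300 | 9% |
| 316 | 10% |
| 400 | 16% |

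**From R² to power.** The standardized effect becomes 0.4 / √(1−R²), with 100 per arm, two-sided 0.05, noncentral t:

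| R² | Power | Equivalent unadjusted N = 200/(1−R²) |
|---|---|---|
| 0% | 80.4% | 200 |
| 1% | 80.8% | 202 |
| 4% | 81.9% | 208 |
| 5% | 82.3% | 211 |
| 9% | 83.9% | 220 |
| 10% | 84.3% | 222 |
| 16% | 86.7% | 238 |

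These are upper values, because they treat the new covariate as unrelated to NRS score and ONS density, which the model already contains. The two degrees of freedom spent do not change power by as much as 0.1 point.

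**Chance imbalance.** With 100 per arm and no stratification by department, the probability that the department share differs by 10 points or more between arms is 18% at a 50:50 mix and 14% at 30:70 (binomial). At an assumed ward gap of 200 kcal/day, a 10-point imbalance moves the unadjusted estimate by 0.10 × 200 = 20 kcal, against a standard error of 70.7 kcal.

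**The case against.** The strongest reply is that nothing here is wrong. Adjusting for the factors used in stratification is a coherent, standard choice, and further covariates could be left to an analysis plan that is not shown. That stands as an answer to any charge of error. It does not make the suggestion empty, because the article names its covariates and says that all analyses use those two.

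A reader might infer that the wards themselves use different requirement formulas, or that their patients are known to differ in age or intake. The article does not say so. The formula follows age and BMI, and only the difference in stay is stated. Stay is also partly dealt with already: intake is divided by the days assessed, and LOS is analyzed in medical inpatients only. Department is therefore the weaker candidate.

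A reader might also infer that the comparison is biased or the trial underpowered. Neither follows. Randomization makes the estimate unbiased on average, the standard error already allows for chance imbalance, and the stated sample size reproduces.

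It can be said that dividing by each patient's own requirement already takes account of age. On the kcal scale the formula does not enter at all, so the age-step argument does not apply there. On the percentage scale, the division creates a step at 65 unless older patients eat about 11% more (2250/2025) at the same weight.

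Finally, the larger gains need ward gaps well above the 200 kcal/day treatment effect. That is correct and limits what can be claimed.

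**Conclusion.** This is an optional, nearly costless improvement. Type I error, freedom from bias and the sample size of 200 are unaffected. The gain is zero if neither age nor department predicts the outcome. It is about 2 power points (80.4% to 82.3%) at R² of about 5%, which the Table 3 age step alone nearly reaches on the percentage scale under an even age split. It is about 4 points only if R² reaches 10%, which for department means a ward gap of roughly 300 kcal/day. The age split, the department split and every ward difference in intake are assumptions. The age step and the covariate list come from the document.

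The differing accounts of the primary analysis in the Abstract and in the section Primary analysis should be settled at the same time, because an unadjusted t test would forgo the gain even from the two factors already planned.

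**What to change.** Keep the randomization as it is. Before any outcome data are analyzed by arm:

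1. Prespecify age and department as covariates, beside NRS score and ONS energy density, in the regressions for energy, protein and ONS intake and in the repeated-measures models. State the form in which age enters; a cut at 65 matches the step in Table 3. Department does not apply to LOS, which is assessed in medical inpatients only.
2. State that the adjusted regression estimate with its 95% confidence interval is the primary result, in line with the Abstract, and that the unadjusted t test is supportive.

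The cost is a sentence or two in the analysis plan and two model degrees of freedom out of 200 patients. Both variables are already collected. Recruitment was still under way at the article's last count (126 participants), so the change could still be prespecified then; made after the outcome data are seen, it would look data-driven.

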**Fig. 1 Fig1:**
[figure not shown]
Patients’ flow. NRS 2002, Nutritional Risk Screening 2002; ONS, oral nutritional supplement; RD, registered dietitian; SAE, serious adverse event

**Table 2 Tab2:** Time schedule for participants

Study period	Screening	Intervention period					Evaluation	Follow-up
Visit	1	2	3	4	5	6		
Day	0	1	8	15	22	29	*	**
NRS 2002 total score	x							
NRS 2002 subscore nutritional status	x							
Inclusion and exclusion criteria	x							
Information, informed consent	x							
Assignment to study group		x						
Baseline patient characteristics		x						
Energy intake/day (kcal)**		Continuous assessment						
Protein intake/day (g)**								
ONS intake/day (ml)**								
Serious adverse events (SAE)**								
Handgrip strength (kg)		x	x***	x***	x***	x***		
Body weight (kg)		x	x***	x***	x***	x***		
Body height (cm)		x						
BMI (kg/m^2^)		x						
Appetite (VAS)		x	x***	x***	x***	x***		
Nausea (VAS)		x	x***	x***	x***	x***		
Procedural variables							x	
Hospital LOS (d)							x	
30-day mortality (y/n)								x

*After patient dismissal or after 30 days of inclusion

**For 30 days upon inclusion

***Assessment at day 1, day 8, day 15, day 22, and day 29

Visits 2–6: study visits may be conducted earlier or later by a maximum of 2 days

The criteria for ONS discontinuation are:
ONS is not indicated anymore due to increased food intakeOccurrence of a serious adverse event (SAE) that necessitates a halt to the prescription

The reasons for discontinuation are documented. Furthermore, withdrawal from the trial is possible at any time at the patients’ request.

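### The models for handgrip strength, weight, appetite and nausea are worded as comparisons of course or change and give the day-1 value no stated role as baseline; conditioning on it would gain precision, mainly for the two VAS scales (minor)

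*Protocol article*

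**What the plan says.** The Primary analysis section of the protocol article states: "Repeated measure models will be used for the evaluation of differences in course of handgrip strength". The same sentence goes on to changes in weight and to the course of appetite and of nausea. The Outcomes section also describes these measures by their course.

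Table 2 schedules all four measures with the footnote "Assessment at day 1, day 8, day 15, day 22, and day 29", so day 1 is the first of up to five assessments. The table also places group assignment at visit 2 (day 1) and lets visits 2 to 6 move by up to two days either way.

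On covariates, the Discussion says that "therefore all statistics will be adjusted for both stratification factors". Those factors are the NRS 2002 score and the energy density of the supplement. The day-1 value of the outcome is neither listed as a covariate nor excluded. The Subgroup analyses section does use day-1 appetite, nausea and handgrip strength, but only to define subgroups for the intake outcomes.

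**The concern.** The sentence names what is to be compared: a difference between arms in a course that begins on day 1, or in a change. The ordinary reading is an arm-by-time contrast with day 1 as an unconstrained first outcome. In a randomized trial the expected values before treatment are equal in the two arms. A change contrast does not use that fact and carries the whole day-1 measurement noise into the treatment estimate. The cost is largest where a patient's scores correlate weakly over time, which is plausible for a VAS that asks only about the current day. A chance day-1 difference d also shifts the estimated change by −(1 − r)d, in the opposite direction.

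Appetite is not a peripheral outcome here. The Background raises the possibility that supplements suppress appetite and so displace food, which is why total intake is studied at all. Follow-up may also be thin. Eligibility requires an expected stay of only three days after screening, and study visits run until discharge. With the two-day window, a patient discharged before day 6 contributes no post-baseline value. The article does not say how many such patients to expect.

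**Working it through.** **The plan's own figure.** The only power statement concerns the primary outcome: "we need to include 200 patients to achieve 80% power", for a difference of 200 kcal/day, SD 500 kcal, alpha 0.05, and "The allocation ratio of intervention group and control group is 1:1". Normal approximation, two-sided: n per arm = 2 × (1.960 + 0.842)² × 500² / 200² = 98.1, so 99 per arm and 198 in total. This reproduces 200; power at 100 per arm is 80.7% (80.4% with the t distribution). The article gives no SD, target difference, correlation or precision for the four outcomes considered here.

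**Inputs for the comparison.** From the article: day 1 plus up to four later visits, 1:1 allocation. Assumed: equal SD s at each visit, and correlation r between day 1 and follow-up.

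**One post-baseline visit.** Per-patient variance entering the arm contrast:

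- change, or unconstrained arm-by-time: 2s²(1 − r)
- adjusted for the day-1 value: s²(1 − r²)
- ratio adjusted/change: (1 + r)/2, so the variance saved is (1 − r)/2

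| r (assumed) | change / s² | adjusted / s² | variance saved | SE reduction |
|---|---|---|---|---|
| 0 | 2.00 | 1.00 | 50% | 29.3% |
| 0.3 | 1.40 | 0.91 | 35% | 19.4% |
| 0.5 | 1.00 | 0.75 | 25% | 13.4% |
| 0.6 | 0.80 | 0.64 | 20% | 10.6% |
| 0.9 | 0.20 | 0.19 | 5% | 2.5% |
| 0.95 | 0.10 | 0.0975 | 2.5% | 1.3% |

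A 25% variance saving corresponds to 1/0.75 = 1.33 times the patients for that outcome.

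**Mean of k post-baseline visits, compound symmetry.** Change: (1 + (k − 1)r)/k + 1 − 2r. Adjusted: (1 + (k − 1)r)/k − r². For k = 4:

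- r = 0.3: 0.875 against 0.385, saving 56%
- r = 0.6: 0.500 against 0.340, saving 32%
- r = 0.9: 0.125 against 0.115, saving 8%

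These apply only to patients who stay for all four later visits.

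**Does the choice of repeated-measures model matter?** Variance of the day-8 arm effect by generalized least squares, 100 per arm, SD 1, r = 0.5:

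- day 1 as an unconstrained first outcome: 0.0200
- day 1 as a first outcome with a common mean in both arms: 0.0150
- day 1 as a covariate: 2 × (1 − 0.25)/100 = 0.0150

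The loss is therefore 25% under the first model and zero under the other two. All three can be called repeated-measures models.

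**If day 1 is measured after supplements have started.** Suppose an early effect e is already present in the day-1 value. The change contrast subtracts e in full from the later effect; the adjusted contrast subtracts r × e. Adjustment is the less affected of the two, but neither is clean.

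**The case against.** The strongest reply is that the article is silent on baseline handling and has not decided against it. A model with a common day-1 mean is itself a repeated-measures model of differences in course, so the quoted sentence permits the remedy, and under that model nothing is lost. Adjusting for the stratification factors does not rule out further covariates. Model detail of this kind for secondary outcomes is often left to the analysis plan, which is not shown. This stands: a reader might infer that the protocol chose change scores over baseline adjustment, and the text does not establish that. What remains is that the article does name the contrast and does name covariates, and taken at its word leads an analyst to the less efficient version.

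A reader might also take a loss of 20% to 35% as a property of this trial. It is not. It is a variance figure that needs r between 0.3 and 0.6, one post-baseline visit and an unconstrained contrast; the article supplies none of these. Nor does the loss apply evenly to four outcomes: if r is near 0.9 for handgrip and weight, it is about 5% with one post-baseline visit.

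A third inference would be bias. The shift described above is conditional on a chance imbalance. Over randomizations the change contrast is unbiased and its test is valid.

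Finally, the visit-2 window means that some day-1 values may be taken after the first supplement portion, so equal day-1 means are not guaranteed. This qualifies the common-mean constraint and belongs in the fix. It does not favour the change contrast, which removes more of any early effect.

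**Conclusion.** Minor. The planned contrast for the four course outcomes is valid but, read plainly, does not use the day-1 value as efficiently as it could. With equal SDs and one post-baseline visit, conditioning on day 1 would save (1 − r)/2 of the variance. For assumed r from 0.3 to 0.6 that is 35% to 20%, or about 19% to 11% of the standard error; at r = 0.9 it is 5% of the variance. It is zero if the intended models already condition on baseline. The practical gain lies with appetite and nausea, on the assumption that single-day VAS scores correlate only moderately over time. The documents do not support saying that the comparison is biased, that any particular percentage is lost, or that the primary outcome or the sample size of 200 is affected.

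**What to change.** In the Primary analysis section, replace the sentence on course and change for these four outcomes with one that specifies a mixed model on the post-day-1 values, with the day-1 value, visit, visit-by-arm and both stratification factors as terms. The equivalent model with day 1 as a first outcome and a common mean in both arms is also acceptable. Report the adjusted arm difference at each visit, starting with day 8, where the fewest patients will have been discharged.

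Add that only day-1 values measured before the first trial supplement portion count as baseline, or that a sensitivity analysis will check the effect of later ones.

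The cost is one or two sentences. No new measurements or visits are needed, provided that the timing of the day-1 assessment relative to the first portion can be recovered from the records. If the analysis plan already conditions on day 1, a cross-reference is enough.
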